### Statistical analysis plan

#### Primary outcomes

Repeated Mixed Models (RMMs) will be used to compare duloxetine to placebo in changes from baseline to treatment for PPTs, cPDT, cPTT, TSP, and CPM. Different variance-covariance structures will be explored using secondary outcomes. Regression analysis using primary and secondary outcomes will be explored to predict the analgesic effect of duloxetine.

#### Secondary outcomes

The secondary efficacy analyses involving duloxetine comparison with placebo will use the secondary outcomes listed above.

The secondary efficacy measures will be analyzed using an RMM approach and potentially covariates will be included. If the RMM analysis shows a significant effect for a variable, contrasts will be constructed for that variable to provide a post hoc pairwise comparison for each time point. Furthermore, on an exploratory basis, pairwise comparisons may be carried out between duloxetine and placebo at each time point.

Analyses focused on responders and non-responders will be conducted for all study parameters with the responder being defined as a minimum reduction in pain from baseline to follow-up after duloxetine intervention of 30% or 50%.

In addition, predictive models using pretreatment parameters will be used to predict the response rate of the duloxetine intervention.

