## Methods and Analysis

### Study design

This proof of concept study is a randomized, placebo-controlled, double-blinded, crossover trial, which compares PPTs, TSP, and CPM before and after 18 weeks of duloxetine and placebo. Forty patients will be randomized to one of two equally sized sequences: (1) duloxetine followed by placebo or (2) placebo followed by duloxetine (Fig. 1). Patients will be screened for inclusion (visit 1) and assessed at baseline (visit 2 and visit 4) and after the intervention (visit 3 and 5).

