### Inclusion criteria and exclusion criteria

#### Inclusion criteria

Patients diagnosed with unilateral or bilateral OA of the knee according to the American College of Rheumatology (ACR) criteria based on clinical and radiographic evidence [1] will be recruited. In addition, patients must provide written informed consent and abide by the study restrictions. The patients must have a Kellgren and Lawrence grade of I, II, or III at the index knee. Worst pain within the last 24 h must be 5.0 cm to 10.0 cm (assessed on a 0–10-cm VAS scale anchored at 0 cm: no pain and 10 cm: worst pain imaginable) prior to enrolment. patients must agree to maintain the same activity level throughout the course of the study.

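### The responder label and the response-prediction model use only the duloxetine period, so as written they cannot separate predictors of drug benefit from predictors of improvement on any treatment

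*Protocol article*

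**What the plan says.** The Secondary outcomes part of the Statistical analysis plan section announces responder and non-responder analyses, with the "responder being defined as a minimum reduction in pain from baseline to follow-up after duloxetine intervention of 30% or 50"%. It adds that "predictive models using pretreatment parameters will be used to predict the response rate of the duloxetine intervention". Both sentences tie the outcome to the duloxetine period, and neither mentions placebo.

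The design supplies the missing contrast. Under Study design, patients are randomised to one of two sequences, "1) duloxetine followed by placebo or (2) placebo followed by duloxetine", and are "assessed at baseline (visit 2 and visit 4) and after the intervention (visit 3 and 5". Each period therefore has its own baseline and follow-up.

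Placebo is used elsewhere in the same plan. Under Primary outcomes, "Repeated Mixed Models (RMMs) will be used to compare duloxetine to placebo in changes from baseline to treatment", and the secondary measures are compared by the same kind of model. That part also says that "Regression analysis using primary and secondary outcomes will be explored to predict the analgesic effect of duloxetine", without defining the analgesic effect.

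Under Clinical implications, the Discussion says that the trial will further demonstrate whether a link between quantitative sensory testing (QST) and drug response exists in osteoarthritis.

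**The concern.** A percentage fall in pain over one treatment period adds together the drug effect, the placebo response, natural fluctuation and regression to the mean. Without the placebo period the label cannot divide these. A baseline variable that predicts the label may be purely prognostic: it may mark patients whose pain falls whatever capsule they take.

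What is at stake is the reading of a positive result. If baseline conditioned pain modulation or temporal summation predicted the duloxetine-period label, the natural report would be that QST identifies duloxetine responders. The same result could arise with no drug effect at all, provided the measure is prognostic for pain change. The within-patient contrast that would settle the question is the main strength of a crossover, and these two analyses leave it out.

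**Working it through.** **1. The plan's own figure.** The Sample size section gives 32 patients for effect size 0.55, 85% power and a 0.05 level. A two-sided paired t-test with standardised within-patient difference 0.55 gives N = 32 with power 85.4%. The normal approximation, ((1.960 + 1.036)/0.55)² = 29.7, gives 30. The figure reproduces and is not disputed. It matters here only as the source of the 0.55 used below.

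**2. How often the label is met without a drug effect.** Assumptions, none of them in the article: baseline pain 6.5 cm, normally distributed change, mean placebo-type fall m of 1.0 to 2.0 cm, SD s of 2.0 or 2.5 cm.

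P(label) = 1 − Φ((c × 6.5 − m)/s), with c × 6.5 = 1.95 cm at the 30% cut and 3.25 cm at the 50% cut.

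| m (cm) | s (cm) | 30% cut, no drug effect | 50% cut, no drug effect | 30% cut, 0.55 SD added |
|---|---|---|---|---|
| 1.0 | 2.0 | 0.32 | 0.13 | 0.53 |
| 1.5 | 2.0 | 0.41 | 0.19 | 0.63 |
| 2.0 | 2.0 | 0.51 | 0.27 | 0.72 |
| 1.0 | 2.5 | 0.35 | 0.18 | 0.57 |
| 1.5 | 2.5 | 0.43 | 0.24 | 0.64 |
| 2.0 | 2.5 | 0.51 | 0.31 | 0.72 |

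First row: (1.95 − 1.0)/2.0 = 0.475, upper tail 0.32. With 0.55 SD added, 0.475 − 0.55 = −0.075, upper tail 0.53.

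**3. How many labelled responders would also meet the cut on placebo.** This depends on the correlation of change between a patient's two periods. In a simulation with the same m and s, baseline uniform from 5 to 9 cm, a 0.55 SD drug effect and between-period correlation 0 to 0.75, 30-65% of duloxetine responders at the 30% cut also met it on placebo. At the 50% cut, 13-51% did.

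**4. What this does to prediction.** Simulated with n = 40, between-period correlation 0.5, and a predictor with the same correlation r with pain change in both periods, so that there is no true interaction. The table shows the share of trials with p < 0.05.

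| r | Outcome: duloxetine-period change | Outcome: duloxetine minus placebo change |
|---|---|---|
| 0.3 | 47% | 5% |
| 0.4 | 75% | 5% |
| 0.5 | 92% | 5% |

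A constant drug effect shifts every patient equally and cancels from the correlation, so the table holds for a zero drug effect too.

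These rates are for the continuous change. The plan's label is a yes/no cut, which loses information. At a 50% responder share the correlation shrinks by a factor of about 0.80, to 0.24, 0.32 and 0.40. Fisher's approximation, Φ(atanh(r) × √37 − 1.96), then gives about 32%, 52% and 73%. Uncut, the same formula gives 47%, 73% and 92%, close to the simulation. The problem is smaller with the label but still far above 5%.

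**The case against.** The strongest reply is that these are secondary and exploratory analyses. The stated primary objective is the treatment effect on pressure pain thresholds, temporal summation and conditioned pain modulation against placebo, and that comparison is sound. This stands, and it limits the point. It does not remove it, because the article says that the trial will demonstrate the QST-response link, and the responder and prediction analyses bear most directly on it. An unseen analysis plan is no defence either, since the article states the definition rather than leaving it out.

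Several stronger readings are tempting and are not supported:

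- **The trial cannot answer the question.** The limit lies in the analysis as written. Both periods are measured, so the data allow the contrast.
- **The predictors come from the duloxetine period.** They are pretreatment parameters. Only the outcome they predict is tied to duloxetine.
- **Predicting response is the trial's aim.** The link appears in the Discussion and is not the stated primary objective.
- **The regression under Primary outcomes has the same fault.** Its target is undefined and could be a contrast with placebo.
- **Regression to the mean inflates every duloxetine period.** Entry requires that "Worst pain within the last 24 h must be 5.0 cm to 10.0 cm", but this applies before enrolment. In the placebo-first sequence the duloxetine baseline is visit 4, after a full placebo period and a gap of at least two weeks, so selection-driven regression should largely be over. The placebo-response argument remains for both sequences.
- **Some 60-71% of duloxetine responders would have responded anyway.** Dividing the rates in step 2 (0.32/0.53 to 0.51/0.72) gives that range, but it is a ratio of marginal rates. The share who would also respond on placebo is the one in step 3.
- **The two thresholds and the unnamed pain score are errors.** Both cuts may simply be reported, and a condensed article commonly leaves the choice of score to the full documents.

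**Conclusion.** The point holds in a limited form. The responder label and the model predicting the duloxetine response rate have no contrast with the same patient's placebo period, so a purely prognostic baseline measure could be reported as a predictor of response to duloxetine. The primary analysis and all average duloxetine-placebo comparisons are untouched.

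The sizes are illustrations under inputs that the article does not give. Across the assumed range, roughly a third to a half of patients would meet the 30% cut, and about an eighth to under a third the 50% cut, with no drug effect. The false-prediction rates also require that the baseline measure is prognostic for pain change; the article does not show that any QST measure is. The defect itself follows from the definition and does not depend on these numbers.

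**What to change.** Three changes to the analysis wording:

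1. Report the 30% and 50% responder rates for both the duloxetine and the placebo period, with a paired comparison.
2. Test prediction as a treatment-by-baseline-predictor interaction in the crossover mixed model using both periods, or regress the within-patient duloxetine-minus-placebo change on the predictor.
3. Label any model fitted to the duloxetine period alone as prognostic.

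This needs no extra patients, visits or measurements. The price is precision: interaction estimates from 40 patients will be wide, and the report should say so. Even after the change, one period per treatment can identify predictors of the average treatment difference but cannot separate a patient's true individual response from period-to-period variation.

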### Ethical considerations

Duloxetine has multiple side effects. Therefore, the patients included in the current study are limited by an extensive exclusion criteria list to ensure that included patients tolerate the study drug. The patients are instructed to inform the study personal of any adverse events. Despite the side effects, duloxetine has been documented to provide analgesic effect to patients who are “centrally sensitized” [61], and the results from the proposed study could act as a proof-of-concept study for new pain treatment of patients with OA and who are severely centrally pain sensitized.

Further, the patients will experience pain during the experimental pain sessions, to which they would normally not be exposed. However, patients will be instructed to push a stop button when the pain becomes intolerable and the test will stop immediately. The patients might experience redness or soreness in the hours following the experimental pain tests, but no long-term effects have been reported by using the methods proposed in this protocol [28, 44–46, 51].

A radiological assessment of the knee (an x-ray) is required to determine the eligibility of OA in the patients. This exposes the patients to radiation, which would normally not occur. The radiation mSv dose for x-ray of the knee will be less than 0.1 mSv, which corresponds to a few days of background radiation and causes a negligible cancer risk. Blood samples will be collected in the study, which may cause bruising of the skin and involve a minimal risk of infection. Trained personnel will conduct the procedures and optimal equipment will be used to limit the risk of x-ray radiation and infections during blood samples to an acceptable level.

The patients enrolled will be asked not to use their current analgesics (up to 4000 mg paracetamol daily is allowed) and to use the study drug only. Paracetamol might not be able to render complete pain relief to the patients enrolled and therefore the patients are likely to feel pain (especially during the placebo phase).

### Modification of the protocol

Any modifications to the protocol which may impact on the conduct of the study, potential benefit of the patient or may affect patient safety, including changes of study objectives, study design, patient population, sample sizes, study procedures, or significant administrative aspects will require a formal amendment to the protocol. Such amendment will be agreed upon by trial steering committee and approved by the Ethics Committee and the Danish Medicines Agency prior to implementation.

### Data collection and management

All data collected are entered in RedCap (version 8.10.1, Vanderbilt University, TN, USA) and will be transferred to SPSS (version 25.0, SPSS Inc., Chicago, IL, USA) for statistical analysis.

### Audit and monitoring

The trial is monitored by the GCP-unit, Denmark (https://gcp-enhed.dk/), and the monitor has been appointed by the sponsor. The Danish Medicines Agency and The North Denmark Region Committee on Health Research Ethics may conduct audits which are independent of the sponsor.

### Confidentiality

All datasets will be fully patient-anonymized.

### Dissemination policy

The trial steering committee is responsible for publishing the results regardless of the outcome. The trial steering committee will discuss potential new publications based on the collected material. Authorship is rewarded based on the guidelines from the International Committee of Medical Journal Editors [31].

## Discussion

The increasing prevalence of obesity and the increasing age of the world population are two factors which may be linked to the increasing prevalence of OA [12]. Standard OA treatments such as exercise-based therapy, NSAIDs, and total joint arthroplasty are efficient in many patients with OA. However, it seems evident that a subset of patients does not gain sufficient pain relief from these treatments [13, 14, 53]. Long-term pharmacological treatment of OA pain is problematic due to side effects and opioids are not advised for treatment of OA pain [10], why new treatment options should be considered. Analgesic effects of duloxetine have been documented in OA but is associated with a high risk of side effects [42] and the underlying mechanisms of the analgesic response are widely unknown.

### The underlying mechanisms for the analgesic effect of duloxetine in osteoarthritis

High pain intensity in combination with a low grade of radiological OA seems to apply to a subset of patients with OA who are highly pain sensitive [2, 22]. Emerging evidence suggests that patients with OA and highly pain sensitive might be at higher risk of poor response to exercise-based therapy [27, 40], analgesic effect of NSAIDs [21, 46, 48], and total joint arthroplasty [5, 15, 33, 36, 37, 39, 52, 57–59], which could suggest that patients with OA who are severely centrally pain sensitive do not respond to standard OA treatment.

Preclinical trials have established that serotonin and noradrenaline are important neurotransmitters for descending noxious inhibitory control [7–9, 35]. Duloxetine is a serotonin-noradrenalin re-uptake inhibitor and the analgesic effect may occur through a facilitation of the descending pain inhibitory control system. The human surrogate model for descending noxious inhibitory control as assessed in preclinical studies is CPM [60], although the indirect measurements that can be done in humans can only be considered a proxy for the direct electrophysiological recordings [19]. This trial will assess CPM before and after administration of duloxetine for 18 weeks together with measures of central sensitization (PPTs, TSP) and will thereby be able to demonstrate if the sensitized pain system is modifiable by duloxetine and possibly link these mechanisms to the analgesic effects.

### Patient adherence to protocol

The current study applies a stand-alone intervention of duloxetine or placebo and allows patients to use up to 4000 mg paracetamol daily but excludes the use of NSAIDs. This might challenge the patient adherence to the protocol and the enrollment in the study. In addition, several known side-effects are associated with the use of duloxetine in OA [42] and this can further challenge the adherence to the protocol.

Finally, the study recruitment and participant adherence are limited due to the outbreak of SARS-CoV-2 [29]. Originally, this study planned to enroll 40 patients for a 14-week intervention period, but due to the pandemic the intervention period was extended to 18 weeks (protocol version 6, 3 June 2020) to ensure participant adherence to the protocol.

### Clinical implications

Personalized medicine is focused on providing the right treatment to the right patient. This has not been explored in-depth in patients with chronic pain but evidence suggests that e.g. patients with painful diabetic neuropathies and impaired CPM might benefit from duloxetine [61]. Similarly, a study found that ketamine can reduce TSP in patients with fibromyalgia [25]. Finally, TSP have been used as a marker to identify patients with chronic pancreatitis responding to gabapentinoids [41]. These studies indicate a link between QST and responses to pharmacological interventions and the current study will further demonstrate if this link exists in patients with OA.

## Trial status

The trial is ongoing and is currently recruiting patients. The first patient was enrolled on January 24, 2020, and the last visit of the last patient is expected to take place end of November 2022. This document is based on protocol version 6 of 3 June 2020. The trail was registered with ClinicalTrails.gov (NCT04224584, link: https://www.clinicaltrials.gov/ct2/show/NCT04224584?term=NCT04224584&draw=2&rank=1) on 6 January 2020 and EudraCT (number: 2019-003437-42) on 22 October 2019.

## Data Availability

The data used and analyzed during the trial will be available by contacting the corresponding author on reasonable request. The sponsor will have full access to the completely patient-anonymized dataset.

## Abbreviations

ACR: American College of Rheumatology
cPDT: Cuff pain detection threshold
cPTT: Cuff pain tolerance threshold
OA: Osteoarthritis
OARSI: Osteoarthritis Research Society International
NSAIDs: Nonsteroidal anti-inflammatory drugs
PPT: Pressure pain threshold
TSP: Temporal summation of pain
CPM: Conditioned pain modulation
